## Abstract

Rationale: high premium is placed on infertility in Nigerian culture. Data is limited on its association with emotional problems in Nigeria. Aims: to develop content for a culturally relevant and cost-effective psychoeducational intervention package and to evaluate its effectiveness for reducing symptoms of anxiety and depression. Sample size estimate: Methods and design: a multi-method study design including development and validation (which includes focus group discussions) of an audio-visual tool which will serve as the intervention in a randomized controlled trial. Data will be analyzed with interim and survival analyses. Population studied: one hundred and 138 (68 per group) infertile women attending infertility clinic in Ibadan. Study outcomes: anxiety and depressions scores assessed with the hospital depression and anxiety scale (HADS) at 0, 3 and 6 weeks. Discussion: it is hoped that the use of the audio-visual tool will improve participants depression and anxiety scores and that the tool will be used for education in routine clinic use and community awareness on psychosocial effects of infertility.

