
### Phase II: randomized controlled trial to test the effectiveness of the psychoeducational intervention

**Study design:** a randomized controlled trial with an allocation ratio of 1: 1 will be utilized.

**Study setting:** 1) University College Hospital (UCH), Ibadan, Nigeria: it serves as a referral tertiary center for Nigeria and sub-Saharan Africa. The study will be at the outpatient gynecology clinic of the hospital; 2) Adeoyo Maternity Hospital (AMH), Yemetu, Ibadan, Nigeria: this is a province-owned secondary health care facility.

**Study subjects:** women attending gynecology clinics in UCH or AMH on account of infertility. Consenting participants will be randomized into the intervention and control arms of the study, respectively.

**Eligibility criteria:** women aged 18 years and above, who have been trying to conceive for at least one year, and who do not have any children.

**Interventions:** consecutive, eligible infertility clinic attendees will be invited to participate in the study and informed consent obtained. Sociodemographic data would be collected via a structured questionnaire. Baseline assessment on participants' psychological and emotional state will be collected via Hospital Anxiety and Depression Scale (HADS) [28]. Thereafter, the participants will be allocated into study groups. Participants in the intervention arm will attend the intervention session on a specified date at the facility. The psychoeducational video will be viewed, and immediate feedback will be obtained. Participants in the control arm will also receive the usual treatment offered all attendees at the gynecology clinics - comprising health talks by public health nurses and explanations and counselling provided by the managing physicians. The study´s primary outcomes are depressive and anxiety symptoms. HADS is a self-assessment scale which has subscales that measure severity of anxiety and depression. It is validated for use in medical outpatient clinics. Participants are followed up at three and six weeks; HADS will be administered at both times. Participants will be counseled on the need for follow-up. Recruited respondents in both arms will receive phone call reminders ahead of scheduled clinic appointments to improve attendance and minimize loss to follow-up.

**Sample size estimation:** the minimum sample size was determined using the formula for comparing two means i.e.

$$\text{n=}\frac{2{\left[Z_{1-\alpha /2}+Z_{1-\beta }\right]}^{2}}{\Delta^{2}}$$

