where Δ, effect size =

$$\Delta =\frac{\mu_{1}-\mu_{1}}{\sigma }$$

where Z1-α/2 [α] was set at 5% i.e. 1.96; Z1-β [β] was set at 20% i.e. power at 80% = 0.84 [29]. A moderate effect size of 0.53 was used. A minimum sample size of 57 was calculated. Attrition rate of 20% was incorporated in the calculation and sample size was estimated at 68 women in each group.

**Randomization procedure:** a randomization list of randomly permuted blocks of treatment assignments in blocks of 4 will be prepared by the study statistician, using a computer-generated table of random numbers. The research assistant will open the sealed envelope containing the assigned group after baseline HADS has been administered. The clinical staff recruiting participants and the data analyst will be blinded, as he will receive two spreadsheets of data without knowing which is the intervention arm.

**Data management and analysis:** the data collected will entered into the computer and analysed using IBM SPSS version 23.0. Interim analysis will be carried out using Mann-Whitney-U test to compare independent samples of the intervention and control groups at 0, 3 and 6 weeks. Survival analysis will also be carried out at each time to assess number of cases of depression or anxiety that transited to non-cases (Figure 1). A data monitoring committee is not necessary as there are no interventions bordering on patient safety. There are no issues that might necessitate termination of trial. Malfeasance or adverse events are not applicable in a trial that constitutes audiovisual expert education as the intervention.

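### One undivided 5% test sizes the trial, but two unranked primary outcomes are each compared at two visits under the label interim, with no stated rule for which result decides effectiveness

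*Protocol article*

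**What the plan says.** All references are to the protocol article, Phase II unless noted.

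- **Outcomes (Interventions).** The "primary outcomes are depressive and anxiety symptoms". They are not ranked, and nothing says whether one or both must improve.
- **Visits (Interventions).** "Participants are followed up at three and six weeks; HADS will be administered at both times". Neither visit is named as the primary one.
- **Score analysis (Data management and analysis).** "Interim analysis will be carried out using Mann-Whitney-U test", to "compare independent samples of the intervention and control groups at 0, 3 and 6 weeks". The abstract repeats the label: "Data will be analyzed with interim and survival analyses". No other analysis of the scores is described.
- **Stopping (same paragraph).** "There are no issues that might necessitate termination of trial", and a data monitoring committee is judged unnecessary.
- **Sample size (Sample size estimation).** A formula for one comparison of two means. Alpha "was set at 5% i.e. 1.96"; beta "was set at 20% i.e. power at 80% = 0.84". A single effect size of 0.53, tied to no outcome or visit, leads to 57 per group and, with 20% attrition, 68 per group.
- **Further analyses of the same scale.** Survival analysis of cases becoming non-cases at each time, and chi-square tests of case status at each visit in Table 3.

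**The concern.** The sample size and the analysis paragraph describe different trials. The first has one test at 5%. The second has two primary outcomes, each compared between arms at two follow-up visits, and does not say which of the four results decides the question. A reader of the results could not tell whether a difference in anxiety at 3 weeks alone would count as success. Neither the 5% nor the 80% then belongs to a defined decision rule.

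The label adds to this. An interim analysis precedes a final one and usually serves a decision to continue or stop. Here the 6-week comparison comes at the last visit, no stopping decision is foreseen, and no final comparison of scores follows. The only score analysis in the plan is therefore presented as provisional.

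**Working it through.** **1. Reproduce the stated sample size.** Inputs from Sample size estimation: z = 1.96, z = 0.84, effect 0.53.

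n = 2(1.96 + 0.84)² / 0.53² = 15.68 / 0.2809 = 55.8, so 56 per group against the stated 57. Attrition: 57 × 1.2 = 68.4, stated as 68. The figure reproduces to within one woman per group and rests on one test with alpha undivided.

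**2. Count the tests.** Two outcomes × two follow-up visits = 4 between-arm Mann-Whitney tests. The baseline comparison is left out because it cannot show an effect.

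**3. Family-wise error if any one significant result counts.** Each test is taken at two-sided 5%, an inference from the sample size because the analysis paragraph sets no level. Independent tests: 1 − 0.95⁴ = 18.5%. For correlated tests, four z-statistics were simulated (1,000,000 draws per setting), with one correlation between the subscales and one between the visits. These correlations are assumptions.

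| Subscales / visits | Family-wise error | Multiple of 5% |
|---|---|---|
| 0 / 0 | 18.5% | 3.7 |
| 0.4 / 0.5 | 16.6% | 3.3 |
| 0.5 / 0.5 | 16.1% | 3.2 |
| 0.6 / 0.6 | 15.0% | 3.0 |
| 0.7 / 0.7 | 13.7% | 2.7 |
| 0.9 / 0.9 | 9.8% | 2.0 |

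**4. One visit, two outcomes, either counts.** 1 − 0.95² = 9.8% if independent; 9.1% at a subscale correlation of 0.5 and 8.3% at 0.7.

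**5. Both outcomes must succeed.** At one visit fixed in advance, both tests must pass 5%, so the error cannot exceed 5%. If either visit may be used, provided both outcomes succeed there, the error stays below 5% when the video affects neither outcome. The power changes, though. With 68 × 0.8 = 54 evaluable per group, power for one test is Φ(0.53 × √(54/2) − 1.96) = Φ(0.79) = 0.786. For both, with an effect of 0.53 on each and independent tests, it is 0.786² = 0.62. Positive correlation raises this, but never above 0.786.

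**6. Power at the first Holm step.** Alpha 2.5%, 54 per group, effect 0.53, noncentral t.

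- t-test: noncentrality 0.53 × √27 = 2.75; power 68%.
- Mann-Whitney, efficiency 3/π for normal data: effective n = 54 × 0.955 = 51.6, noncentrality 2.69; power 66%.
- Baseline-adjusted, r = 0.3: effect 0.53/√(1 − 0.09) = 0.556, noncentrality 2.89; power 73%.
- Baseline-adjusted, r = 0.5: effect 0.53/√(1 − 0.25) = 0.612, noncentrality 3.18; power 82%.

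The baseline correlations are assumed. These are the powers of one outcome tested at 2.5%. Holm does slightly better for an outcome that reaches the second step, at 5%.

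**The case against.** **No any-one-wins rule is stated.** This is right, and it limits the claim. A reader might infer that the trial's false-positive rate simply is three times 5%. The article does not support that: each test keeps its own 5%, the inflation is family-wise, and it arises only if one success among several is enough. What stands is that the article fixes neither this rule nor its alternative, and the stated design figures do not carry over to either.

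**The trial is called exploratory, and the detail may sit elsewhere.** Methods does call phase II exploratory, and a multiplicity method may well be in a full protocol or analysis plan that is not shown. This lowers the severity. But the same sentence says the trial is to test effectiveness, the third aim is to evaluate it, and the sample size is confirmatory in form. A separate document could supply a rule, but would not by itself reconcile the one-test sample size and the interim label with the comparisons described here.

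**Interim is only a wrong word.** Largely so. A reader might infer a group-sequential look that spends alpha. The text does not support this, since no stopping decision is foreseen. The label makes the plan unclear; it does not raise the error rate.

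**The other tests would raise the rate further.** A reader might add the chi-square and survival analyses to the family and arrive at a much higher figure. The article does not support one. Table 3 has a single block of cases and non-cases with one chi-square per visit, not split by subscale. The survival analysis is not specified as a comparison between arms, and no case rate is given.

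**Conclusion.** The point holds in a conditional form. The sample size allots one two-sided 5% to one comparison, while the plan makes four follow-up comparisons of two unranked primary outcomes and labels its only score analysis interim.

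If any one of the four may establish effectiveness, the family-wise error is about 14% to 17% at assumed correlations of 0.4 to 0.7, and 10% to 18.5% over the whole range tried. With one visit and either outcome sufficient, it is about 8% to 9% at moderate correlation. If both must succeed at a visit fixed in advance, the error is not inflated, but the stated 80% power is not the power of that rule.

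This should be fixed, but it is not fatal: the article calls the trial exploratory, the success rule is unstated rather than wrongly stated, and the analysis plan is not shown.

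**What to change.** 1. Delete interim from the abstract and the analysis paragraph, and state that the between-arm comparisons are run once, after the last 6-week visit.
2. Name one primary visit, for example week 6, for the HADS anxiety and depression scores, and test the two with Holm at overall 5%. Other choices are defensible, such as ranking the outcomes or requiring both; what matters is that one is fixed before the data are seen.
3. Make the other visit, case status and remission secondary, with no claim of effectiveness resting on them.
4. Restate power for the chosen rule, using the Holm figures above if Holm is chosen.

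**Cost.** The first three changes are wording, but power per outcome falls: to about 66% at the first Holm step with the planned Mann-Whitney test. Baseline HADS is already collected, so adjusting for it needs no new data, but it means replacing the Mann-Whitney test, and it restores about 80% only if the baseline correlation is near 0.5; at 0.3 it gives about 73%. Without adjustment, 80% power at alpha 2.5% needs 68 evaluable per group by the plan's own formula, or 68/0.8 = 85 recruited, against the planned 68 recruited.

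### 68 women per group does not cover 20% attrition from a minimum of 57: 54 remain, and power is about 78% instead of the stated 80%

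*Protocol article*

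**What the plan says.** All the figures are in the Sample size estimation paragraph under Phase II of the protocol article.

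- Method: "the minimum sample size was determined using the formula for comparing two means", for a trial randomised 1:1.
- Type I error: "where Z1-α/2 [α] was set at 5% i.e. 1.96", so the test is two-sided.
- Power: β "was set at 20% i.e. power at 80% = 0.84".
- Effect: "A moderate effect size of 0.53 was used".
- Size before attrition: "A minimum sample size of 57 was calculated".
- Size after attrition: "Attrition rate of 20% was incorporated in the calculation and sample size was estimated at 68 women in each group".

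The abstract describes the population as "one hundred and 138 (68 per group) infertile women attending infertility clinic in Ibadan". Two groups of 68 make 136. A total of 138 would be two groups of 69.

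**The concern.** An attrition allowance exists so that the required number is still there after the expected loss. Here the minimum, the expected loss and the enrolment target are all printed, and they cannot all hold: taking 20% away from 68 gives fewer than 57. The usual cause is multiplying by 1 plus the attrition rate when one should divide by 1 minus it.

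The 80% power is the only justification the article gives for its sample size. Under the protocol's own expected attrition that power is not reached. Any reader can see this by multiplying 68 by 0.8, and the inconsistency would carry into the trial report.

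**Working it through.** **Inputs**, all from the Sample size estimation paragraph unless noted: z for two-sided α of 5% = 1.96; z for 80% power = 0.84; Δ = 0.53; minimum 57 per group; attrition 20%; final 68 per group. From the abstract: total 138.

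**1. The minimum of 57.**
The printed formula gives n = 2(1.96 + 0.84)² / 0.53² = 15.68 / 0.2809 = 55.8, so 56 per group. The exact two-sample t-test needs 56.9, so 57. The stated 57 is therefore reproduced: it is the t-test answer and one above the printed formula. A one-sided test would need 45 and does not fit.

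**2. The step from 57 to 68.**
- Multiplying: 57 × 1.2 = 68.4, which is 68 rounded down or 69 rounded up. Two groups of 69 make 138, the abstract's total.
- Dividing, which is what a 20% loss requires: 57 / 0.8 = 71.25, so 72 per group.
- Dividing from the formula's own 56: 56 / 0.8 = 70.

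The stated 68 matches the multiplication. The article does not show the step, so this is an inference, but the next step does not depend on it.

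**3. What 68 leaves.**
68 × 0.8 = 54.4, so 54 per group. That is below 57, and below 56 as well. The attrition that 68 can absorb is 1 − 57/68 = 16.2% if 57 are needed, or 1 − 56/68 = 17.6% if 56 are needed.

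**4. Power at Δ = 0.53, two-sided 5%.**
By the normal formula, power = Φ(Δ√(n/2) − 1.96). For n = 54 this is Φ(0.53 × 5.196 − 1.96) = Φ(0.794) = 78.6%.

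| Evaluable per group | How it arises | Normal formula | Exact t-test |
|---|---|---|---|
| 54 | 68 enrolled, 20% lost | 78.6% | 77.9% |
| 55 | 69 enrolled, 20% lost | 79.4% | 78.7% |
| 56 | minimum by the printed formula | 80.1% | 79.4% |
| 57 | stated minimum | 80.8% | 80.1% |

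The shortfall from 80% at 54 per group is 1.4 points (normal) to 2.1 points (t-test).

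**5. Detectable effect at 54 per group with 80% power.**
Normal formula: (1.96 + 0.84) × √(2/54) = 2.8 × 0.1925 = 0.539. Exact t-test: 0.544. Either way it is about 0.54, against 0.53 planned.

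**6. Check on 72.**
72 × 0.8 = 57.6, so 57 are kept and the t-test power is 80.1%. That is 4 more women per group than 68, or 144 in total.

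**The case against.** The strongest reply is that this hardly matters. By the protocol's own normal formula the minimum is 56, the size after attrition would be 70, and 68 is only two women short per group. The power lost is one to two points. Follow-up lasts six weeks and phone reminders are planned, so attrition may well stay under 16%. The article also calls the trial exploratory. All of this stands and it limits the weight of the point. It does not remove the contradiction: the article expects 20% loss and says that the allowance was made, yet 54 is below both 57 and 56. Nor is this a detail lost in condensing a full protocol, because the article prints all three figures.

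The abstract's total does not repair it either. At 69 per group, 55 remain after 20% loss, with power of 78.7% (t-test) or 79.4% (normal).

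Two stronger readings are tempting, and the document does not support them.

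- A reader might infer that the trial is seriously underpowered. It is not so on these figures, since the detectable effect moves only from 0.53 to about 0.54.
- A reader might add a further loss because the Data management and analysis paragraph names the Mann-Whitney test, and so put power at about 76%. That figure assumes normally distributed scores, for which the test's relative efficiency is about 0.955. The article gives no distribution for the HADS scores, and with skewed scores the rank test may lose nothing. The article also names that test only under interim analysis, beside survival analysis and, in Table 3, chi-square tests, so it is not clearly the primary test.

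**Conclusion.** Wrong as written, and minor. A minimum of 57, attrition of 20% and enrolment of 68 per group cannot all be true. If 20% are lost, 54 women per group remain and power is about 78% (77.9% by t-test, 78.6% by the normal formula), not 80%. The effect detectable with 80% power is about 0.54. The stated minimum survives only if attrition is 16% or less.

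This rests on the protocol's own inputs (effect 0.53, two-sided 5%, comparison of two means) and on equal loss in the two groups. That 68 came from multiplying 57 by 1.2 is a likely explanation and not an established fact; the conclusion holds without it. The mismatch between 138 and 2 × 68 = 136 is a separate inconsistency, but it bears on which enrolment figure the corrected power statement should use.

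**What to change.** Replace the last sentence of the Sample size estimation paragraph with:

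> 68 women per group with 20% attrition leaves 54 evaluable per group, giving about 78% power for an effect size of 0.53; 57 evaluable women per group are retained only if attrition is 16% or less.

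At the same time, settle the enrolment figure and make the abstract agree with it: 136 in total for 68 per group, or 138 for 69. If 69 is intended, the sentence should say that 55 remain after 20% loss, with about 79% power.

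This costs wording only, and a slightly less favourable power statement. If the sponsor prefers to keep 80% power under 20% attrition, the target becomes 72 per group, which is 8 more women in total than 2 × 68.

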**Figure 1 F1:**
[figure not shown]
program evaluation and review technic (PERT) diagram showing flow of participants into cases or non-cases

**Ethical considerations:** ethical approval was obtained from the University of Ibadan/University College Hospital Ethical Committee (Ref: UI/EC/17/0003). Protocol amendments will be communicated to the ethics committee and written approval obtained before commencing. Clinical care providers in the clinic will recruit the participants and obtain assent, then a trained research assistant will obtain informed consent (Annex 1). Anonymized data will be obtained from participants in privacy and data collected will be kept in a secure locked cabinet in an office. Data entered on to the study computer will be password-protected. Personal information will only be recorded in order to send reminders and invitations for follow up sessions. The investigators will have access to the final data set and will not disclose information to other parties.

**Trial registration:** the trial is registered with Pan African Clinical Trial Registry [PACTR201901892865101].

**Reporting of trial results:**Table 1 will describe the demographics of the participants in the intervention and control groups, while Table 2 will show the proportion of cases to non-cases. The changes in these over 6 weeks will be documented in Table 3 and Figure 1. Trial findings will be communicated in a written report to sponsors, presented at a gynecology conference and published in a per-reviewed journal. The authors will be those who have contributed to the conception, design, data acquisition and writing of the manuscript. The full protocol and dataset will be available by contacting the corresponding author.

**Table 1 T1:** distribution of socio-demographic characteristics of participants

Variables	Classes	Intervention group No [%]	Control group No [%]	p-value
Age	< 35 years			
	≥ 35 years			
Marital status	Married			
	Unmarried			
Education	None			
	Primary/ secondary			
	Tertiary			
Occupation	Unemployed			
	Unskilled			
	Skilled			
Previous pregnancies	Yes			
	No			
Identified cause of infertility	Self			
	Male partner			
	Neither/both/ unknown			
Length of infertility	≤ median			
	> median			
Average monthly family income*	≤ median			
	> median			

**Table 2 T2:** participants diagnosed of depression and anxiety by HADS

Variables	Classes	Anxiety				Depression			
		Control group		Intervention group		Control group		Intervention group	

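### A single fixed block size of 4, with an unblinded research assistant role that both takes consent and opens envelopes, leaves some upcoming allocations open to deduction

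*Protocol article*

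**What the plan says.** All references are to the protocol article, Phase II.

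- **Block size** (Randomization procedure): "a randomization list of randomly permuted blocks of treatment assignments in blocks of 4 will be prepared by the study statistician". Only one block size is given.
- **Opening of envelopes** (same section): "The research assistant will open the sealed envelope containing the assigned group after baseline HADS has been administered".
- **Consent** (Ethical considerations): "Clinical care providers in the clinic will recruit the participants and obtain assent, then a trained research assistant will obtain informed consent".
- **Blinding** (Randomization procedure): "The clinical staff recruiting participants and the data analyst will be blinded". The research assistant is not named there, and nothing says that the block size is withheld from that role.
- **Arms** (Interventions): "Participants in the intervention arm will attend the intervention session on a specified date at the facility". Controls receive the usual clinic talks and counselling, so the arm is evident once it is assigned.
- **Sites** (Study subjects and Study setting): the trial enrols "women attending gynecology clinics in UCH or AMH on account of infertility". The first is a tertiary referral centre. Of the second the article says "this is a province-owned secondary health care facility". How the randomization list is divided between the two is not stated.

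**The concern.** In permuted blocks of known size, past assignments carry information about the next one. The person who opens the envelopes sees the past assignments. Here the same role also takes informed consent from the next woman, after the blinded clinicians have handed her over. Opening the envelope after baseline HADS hides only that woman's envelope; it does not stop inference from the envelopes opened before hers.

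At stake is selection bias. Foreknowledge could affect who is consented and how participation is presented, and the analysis cannot repair that afterwards. An influence on baseline HADS is the weaker route, because the scale is completed by the woman herself.

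**Working it through.** The article gives no predictability figure to reproduce, so the check starts from its design inputs.

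**Inputs.** Block size 4 and the sealed-envelope procedure (Randomization procedure); 1:1 allocation (Study design); 68 per group (Sample size estimation), so 2 × 68 = 136 women, or 136 / 4 = 34 complete blocks.

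**Step 1: share of assignments certain in advance.** A block of two A and two B has 6 equally likely orders. The observer is assumed to know the block size and all earlier assignments in the sequence.
- Positions 1 and 2 are never certain.
- Position 3 is certain when the first two are alike, which happens in 2 of 6 orders = 1/3.
- Position 4 is always certain.
- Share = (0 + 0 + 1/3 + 1) / 4 = 33.3%, and 136 × 1/3 ≈ 45 women.

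**Step 2: correct-guess rate, always guessing the arm that is behind.**
- Position 1: 1/2.
- Position 2: 2/3, since two of the three remaining slots belong to the other arm.
- Position 3: (1/3 × 1) + (2/3 × 1/2) = 2/3.
- Position 4: 1.
- Rate = (1/2 + 2/3 + 2/3 + 1) / 4 = 70.8%, against 50% by chance.

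**Step 3: one list across both hospitals, with the assistant seeing only one of them.** Simulation of lists of 136 in blocks of 4, with women assigned to sites at random, gives a correct-guess rate of 53.0% for a 50:50 site split and 53.8% for 70:30. The article gives no site split, so both are assumptions.

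**Step 4: what varying the block size achieves.** This is a simulation of lists of 136 with blocks of 4 and 6 chosen at random. The observer knows the possible sizes and all earlier assignments.

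| List | Certain in advance | Guessed correctly |
|---|---|---|
| Fixed 4 | 33.3% | 70.8% |
| Random 4 and 6 | about 6% | about 69% |

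The gain is therefore in certainty: block ends are no longer known. The guess rate hardly moves, which is why withholding the sizes and separating the two tasks also matter.

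**The case against.** The strongest case on the other side has five parts.

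1. **Safeguards are already planned.** Eligible attendees are invited consecutively, recruiting clinicians are blinded, envelopes are sealed, and consent and baseline HADS come before opening. This stands as mitigation. It does not close the gap, because consent is taken after the blinded clinicians' step by a role that is not listed as blinded.

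2. **One person in both tasks is not established.** The article writes of a trained research assistant in one section and the research assistant in the other; these may be different people. Nor does it say that this person knows the block size. Both points stand, so the figures are conditional. The article does, however, give the two tasks to the same role and states no separation. A single block size, printed in a published article, is also not hard to learn.

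3. **The 71% may not apply.** It needs sight of the earlier assignments in the same sequence, hence separate lists by hospital or one assistant covering both. Otherwise the rate is about 53-54%. This stands.

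4. **Varying the blocks barely changes the guess rate.** Correct (70.8% to about 69%), but the certain share falls from 33.3% to about 6%.

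5. **A shared list is not stated.** A reader might infer that the two hospitals draw on one unstratified list, since the article speaks of a single list and names two different hospitals. The article does not support that. It is silent on how the list is divided, and a condensed article may leave stratification to the full protocol. Even on an assumed shared list with 68 women per site, the roughly 12% probability that one hospital's arms differ by 10 or more (39 against 29) would describe chance imbalance, not bias. Whether the list is shared is a question for the sponsor.

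**Conclusion.** The concern holds in a limited form. The fixed block of 4, arms that are visible after assignment, and an unblinded role that both takes consent and opens envelopes are all in the text. Together they allow up to one third of assignments to be certain, and up to 71% to be guessed, before consent is taken.

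Those upper bounds assume that the assistant knows or works out the block size, has seen the earlier assignments in the sequence, and is the same person in both tasks. With one list over two hospitals and an assistant at only one, the guess rate is about 53-54%, on assumed site splits.

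A reader might infer that allocation in this trial is in fact 71% predictable, or that selection has been compromised. The article shows neither; it shows an avoidable opening. The change is worth making because it is cheap before recruitment and the bias could not be corrected later. The stated sample size is not affected.

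**What to change.** 1. Generate the list with randomly varying block sizes, for example 4 and 6.
2. Withhold the sizes from anyone who takes consent or opens envelopes, and keep them out of documents that those staff use.
3. Where existing staffing allows, have one person take consent and another open the envelope, and say so in the protocol. Keep the planned order of consent, baseline HADS, then envelope.
4. The sponsor should confirm whether each hospital already has its own list. If not, generate the list by hospital with the same varying blocks. Separate lists with a fixed block of 4 would restore the full predictability to an assistant at a single site, so this step should not be taken without the first two.

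**Cost.** A new computer-generated list and a sentence or two on roles. The final split may be slightly unequal: an unfinished block of 6 can leave the arms at most 3 apart on each list, so at most 2 × 3 = 6 over two hospital lists.
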